## Appendix A: Project Description

### Comprehensive Cervical Cancer Prevention in Tanzania (CONCEPT)

#### 1. Project Summary

The natural history of Human papillomavirus (HPV) in sub-Saharan Africa is not yet fully understood. As persistent HPV infection is a necessary factor in development of cervical cancer – a major health problem in sub-Saharan Africa – information about how HIV together with other risk factors interacts with HPV acquisition and HPV persistence/clearance is warranted. Additionally, concern prevails about the quality of cervical cancer preventive strategies in sub-Saharan Africa. Against this background the project aims to provide a better understanding of the natural history of HPV with a view to HIV status, to measure the impact of a novel and simple screening method based on *CareHPV* testing and to assess how continuity of care among women who are tested HPV positive can be improved. The study will be linked up with the existing cervical cancer screening program at Ocean Road Cancer Institute (ORCI) and Kilimanjaro Christian Medical Centre (KCMC); and will include 4000 women who are attending screening service or HIV care and treatment. HPV acquisition and persistence/clearance patterns as well as the absolute risk of severe cervical precancerous lesions will be determined through a follow up study lasting 28 months. The test performance of *CareHPV* testing, liquid-based cytology and VIA will be described and the operating characteristics of the three screening methods will be assessed according to HIV status. Finally, the impact of a mobile phone intervention and a patient navigation model will be assessed and compared according to the proportion of HPV positive women who return for follow-up examinations. Additionally, the project will implement a research capacity building component focusing on transfer of knowledge and technology as well as training of PhD students. The activities will be carried out as five sub-studies: i) HPV acquisition pattern; ii) HPV persistence/clearance pattern; iii) Test performance of *CareHPV* testing, liquid-based cytology and VIA; iv) Continuity of care among screened positive women and v) research capacity building as well as transfer of knowledge and technology

#### 2. Objectives

With the overall aim of substantially improving cervical cancer prevention in Tanzania and thereby reduce mortality, the CONCEPT project focuses on the natural history of human papillomavirus (HPV), which is the most important risk factor for cervical cancer.

HPV can take the form of being either a transient infection, that relatively rapidly is cleared by the host immune system or it can become a persistent infection that may progress to high-grade cervical lesions or cervical cancer (**Fig. 1**). In spite of the fact that cervical cancer is the most common malignancy among women in Sub-Saharan Africa (1), little is known about the distribution of HPV types, risk factors of incidence and patterns of persistence for different HPV types. The proposed project will address this lack of knowledge and provide new information about the natural history of HPV and consequences of HPV infection among HIV positive and HIV negative women. In addition, there is concern about the performance of the screening approaches applied in many sub-Saharan African countries and information on the quality of novel, affordable screening approaches that will perform well in remote areas is warranted. Finally, in many sub-Saharan African settings worries prevail about lack of continuity of care among women who are diagnosed with precancerous lesions and therefore relevant treatment is not always offered. The proposed project will address these shortcomings in cervical cancer prevention. The research will build on the results previously obtained by our research team (2-6) and will be innovative in the way that it through a comprehensive approach will use the natural history of HPV to identify opportunities to strengthen and further develop the existing screening program in Tanzania, with a particular view to the importance of HIV positivity. In addition, with the aim to bridge the gap in continuity of care among women diagnosed with precancerous lesions, the project will develop and test a reliable and sustainable communication system through a multidisciplinary approach, involving community education, social mobilization and use of cell-phones. Thus the proposed study has the potential to produce results with immediate public health impact.

The specific objectives of the project are:

1. To assess acquisition patterns and incidence of HPV infection with a specific focus on differences in HPV acquisition, distribution of HPV types and risk factors among HIV positive and HIV negative women
2. To assess persistence of high-risk HPV infection with a specific focus on whether there are differences in HPV persistence in relation to specific HPV types and differences in risk factors for HPV persistence among HIV positive and HIV negative women. In addition, it is the aim to examine the absolute risk of HSIL or worse in relation to both one time HPV positivity and HPV persistence while taking HIV status into account
3. To evaluate the performance of Self collected *CareHPV* testing, health provider collected HPV test, Pap smear (liquid-based cytology) and visual inspection with acetic acid (VIA) for detection of cervical precancerous lesions with a special view to test performance among HIV positive and HIV negative women.
4. To evaluate and compare two different interventions aiming at ensuring continuity of care among women who are tested HPV positive in terms of effect and costs, and to describe barriers for not adhering to the scheduled follow-up
5. To enhance research capacity and transfer of knowledge and technology through the training of PhD students and the involvement of a post-doctoral fellow

### 3. Project's methodology

Based on the experience and success of our previous study of HPV prevalence in Tanzanian women, the present study will be linked up with the existing cervical cancer screening program in Dar es Salaam and Kilimanjaro Region. To make sure that we will include enough HIV positive women into the study, we will oversample HIV positive women. This will be done through enrolment of women attending HIV care and treatment in the two study areas. A total of 4000 women will be enrolled at baseline in the study - 3500 women from the two screening settings and 500 HIV positive women from two HIV care and treatment clinics. Based on our previous experience, among the 3500 women recruited from the screening settings, around 700 will be high-risk (HR)-HPV positive and nearly 350 women will be HIV positive (2). Among the 500 HIV positive women recruited from the HIV clinics, an estimated 250 women will be HPV positive (2). Hence, the total study sample of 4000 women will include an estimated 950 HPV positive and 850 HIV positive women. A power calculation was based on McNemars test in the situation where we compare two diagnostic tests (1: standard test (VIA) vs 2: new test (*CareHPV*)) where the outcome is sensitivity  $S_1$  and  $S_2$ , respectively. Based on our previous studies in Tanzania (4) it is estimated that 180-200 women will have precancerous lesions at baseline (~true positive), and we assume a significance level of 5% and that the sensitivity of the standard test is  $S_1=30\%$ . We will then with 80% power be able to detect a significant difference if the sensitivity of the new test is at least  $S_2=44\%$ . As we anticipate *CareHPV* testing to have a much higher sensitivity, we will have sufficient power in the present study

An overview of the study design is outlined in **Fig. 2**. In principle the study comprises a baseline visit and 2 follow-up visits:

At **baseline** we will collect on all participating women a cervical sample for *CareHPV* testing, a novel and simple quick test for detection of HPV. We will also obtain a liquid-based cervical swab (ThinPrep) for cytology examination (subsequently prepared and diagnosed in Denmark), high-risk Hybrid Capture (HC2) testing (in Germany), and genotyping (PCR-based HPV testing in Germany). Following this, VIA will be done with 5% acetic acid. The Tanzanian staff will receive training (re-training) in sample collection and VIA before start of the study by national trainers according to IARC guidelines. In case of a positive cytology (HSIL or worse) the woman will be called in and will be treated according to the cervical cancer screening standard of care methods in Tanzania. Similarly, all VIA positive women will be treated according to the cervical cancer screening standard of care methods in Tanzania. Information on socio-economic characteristics, lifestyle factors and reproductive history will be recorded through a personal

interview, and blood samples for HIV testing will be obtained. Before the initiation of the study, the staff in Tanzania will receive training in *CareHPV* testing. The *CareHPV* (including currently known HR-HPV types 16, 18, 31, 33, 35, 39, 45, 51, 52, 56, 58, 59, 66, and 68) will be tested within 14 days in Tanzania. At the **first follow-up**, taking place 14 months after inclusion, a randomly selected sample of 500 women will be trained on self-collection of a cervical swab for HPV testing. Thereafter another cervical swab (ThinPrep) will be collected (on all study subjects in the 1st follow-up) by a trained health provider. At the **second follow-up**, taking place 26 months after inclusion, a cervical swab (ThinPrep) will be obtained from each woman. Women who do not return to the clinic for first and second follow-up will be traced and visited at home and invited to attend the clinic for screening. If they do not wish to re-attend, they will be offered screening through a self-collected HPV sample. We anticipate a response rate in the 1st follow-up at 90% and a response rate in the 2nd follow-up at 80%. The anticipated follow-up rate is based on experiences from previous follow-up studies in Tanzania(7). The study is grouped in five work package according to the specific objectives:

**Work package 1, Acquisition patterns of high-risk (HR) human papillomavirus (HPV) with a special view to HIV status:** Among women testing HR-HPV negative at baseline (Fig. 2), all women testing HIV positive (~190 from the screening clinic and 250 from HIV clinics = 440 in total) as well as a random sample of 560 HPV negative/HIV negative women will be invited to a new gynecological examination after 14 months (1st follow-up visit), where a health provider cervical swab (ThinPrep) sample on all women is taken. These samples will all be tested for HPV using HC2 and genotyping will be performed on the HPV positive samples. At the 2nd follow-up visit (at 26 months) a health provider taken cervical swab (ThinPrep) will be obtained. All samples from the 2nd follow-up will be sent to Denmark for establishment of a cytology diagnosis and the remaining material will be sent to Germany for HC2 testing and subsequent genotyping of the HPV positives. All cytology results and HPV results will be sent back to Tanzania. In case of a positive cytology (HSIL or worse) the woman will be called in and will be treated according to the cervical cancer screening standard of care methods in Tanzania.

Based on the literature (8) we estimate an HPV acquisition rate among the initially HPV negative women at 1st follow-up of around 10%, similarly an acquisition rate of 10% from the 1st to the 2nd follow-up. The association between HR-HPV acquisition and the women's age, life style characteristics, reproductive history and HIV status will be assessed.

**Work package 2, Persistence patterns of high-risk HPV types and absolute risk of severe cervical lesions focusing on the importance of HIV status:** Persistence/clearance patterns of HR-HPV will be determined among all women who are HR-HPV positive at baseline (Fig. 2) (~700 from the screening clinic and 250 from the HIV clinic i.e. ~950 in total). They will be invited for follow-up examinations and tested for HR-HPV after 14 and 26 months (1st and 2nd follow-up visit). For this group of women also a self-collected cervical swab will be obtained at the 1st follow-up in 500 randomly selected women. HPV genotyping will be performed among women who are HR-HPV positive during follow-up. Women who are persistently HPV positive for the same HPV type at enrolment and at 1st follow-up will be called in for a cytological examination at the respective clinic. Also in case of a positive cytology (HSIL or worse), the women will be called in for further follow-up. HR-HPV persistence/clearance patterns will be described in relation to the women's age, life style characteristics, reproductive history, HIV status and HPV genotype. We estimate a persistence rate of 40% after 14 months and of 20% after 26 months (9). Due to the fact that a cytology diagnosis is obtained on all women at the 2nd follow-up, we will also be able to look at the absolute risk of HSIL or worse in relation to both one time HPV positivity, HPV persistence and according to HIV status.

**Work package 3, Test performance of CareHPV testing, pap smear and VIA for detection of cervical precancerous lesions:** As described above, all 4000 women enrolled will be screened by use of *CareHPV* testing, Pap smear (liquid based cytology i.e. ThinPrep) and VIA at the study baseline, and the sensitivity and specificity of *CareHPV* testing and VIA will be estimated and the positive and negative predictive values calculated. The operating

characteristics of the two screening methods will be assessed according to HIV status. All VIA positive women will subsequently be treated in agreement with the cervical cancer screening standard of care methods in Tanzania. In case of a positive cytology that was not already identified through a positive VIA, the women will be called in for further follow-up. High-quality cervical liquid-based cytology and where possible also cervical biopsies will be used as Gold Standard. Based on the samples collected at the 1st follow-up, the HPV results from the self-collected brush and the health provider collected brush will be compared.

**Work package 4, Continuity of care among women who are tested are HPV positive – a comparison of two different interventions:** Women who are tested HPV positive at enrolment will be randomized to either a patient navigation model or a cell phone model consisting of automated SMS messages. *Patient navigation model:* A trained community health worker will be identified as the woman's patient navigator. There will be established a one-to-one relationship between the patient navigator and the woman to address anticipated barriers such as communication difficulties and difficulties with arranging transportation. *Cell phone model:* HPV positive women will receive automatically generated SMS messages, which will convey HPV result, send appointment reminders and health information during the first 12-14 months follow-up period. After 20 months, the continuity of care, based on the number of HPV positive women who return for the 1st follow-up examination after 14 months, will be compared. Additionally, the average time spent providing navigation from an HPV positive result is established to 12-14 months after and the associated cost will be calculated. Likewise the price of establishing and maintaining the system generating the SMS reminders will be measured. The differences in total costs and re-attendance between patient navigation and SMS reminders will be calculated. Re-attendance will be defined as HPV positive woman who re-attend within 12-14 months after the HPV positive result is established. Finally, HPV positive women who do not re-attend for screening after 12-14 months will be traced and interviewed. A mixed method approach, relying on structured questionnaires, in-depth interview and key informant interviews will be used to describe perceived barriers for attending 12-14 months follow-up.

**Work package 5, Health service capacity building for cervical cancer prevention:** Health service capacity building will be performed at primary, secondary and tertiary level. At the primary and secondary levels, key barriers for optimal use of existing communication paths for ensuring continuity of care among women diagnosed with precancerous lesions will be identified through a register based desk study. Based on the results, interview guides will be developed for in-depth interviews with health providers working at primary and secondary level and community representatives. The experiences from this assessment will be used to develop a training program in cervical cancer prevention and patient navigation that will include staff at primary and secondary health units together with community health workers in Dar es Salaam and Kilimanjaro Region. The trained community health worker will be employed as patient navigators. At tertiary level, the project will respond to the research needs set forth by ORCI and KCMC. Three PhD courses, one in Clinical Trials, one in Prevention and Control of Gynaecological Cancers and one in Policy Brief Writing will be offered at KCMC in alignment with the exiting BSU initiatives at KCMC. The PhD courses will be co-developed and co-taught by Tanzanian and Danish researchers. At both ORCI and KCMC there is a need to strengthen the capacities of researchers to undertake in-country PhD training at an international level. To address this need, four PhD studies, three Tanzanian and one Danish (co funded by SDU), will be included in the project. The Tanzanian PhD students will be recruited through public announcement of the scholarships and competitive applications. Two of the Tanzanian PhD students will be enrolled at KCMC and one at ORCI. They will additionally conduct 3 months of academic work each year in Denmark. The project will be performed as a twinning arrangement where the Tanzanian and the Danish PhD students will work closely together. To increase the expertise within HPV epidemiology and HPV testing in Tanzania and thereby increase the sustainability of the project outcomes, a post-doctoral fellow, [name] (CK), who has obtained his PhD as part of our previous research (2-6, 9) and who is presently acting as national trainer for the cervical cancer

prevention program in Tanzania, will be employed in the project. He will be visiting Institute of Medical Virology at Tuebingen University in Germany to get detailed knowledge about HPV testing and HPV analyses. In addition, to enhance local expertise in cervical cancer screening and HPV testing, a faculty exchange to the International Agency for Research on Cancer (IARC) in Lyon will also be arranged. Finally, to further upgrade CK's academic skills he will be involved as a co-supervisor of the two PhD projects focusing on Cervical Cancer Screening and Continuity of Care and write two independent papers based on the research findings.

Ethical research permissions will be obtained from the Ministry of Health in Tanzania and from local authorities in Dar es Salaam and Kilimanjaro. Ethical clearance will be obtained from the Ethical Review Board at KCMC and ORCI as well as from the Ethical Review Board of the National Institute of Medical Research. The project will follow the international ethical guidelines developed by CIOMS (Council for International Organization of Medical Sciences), placing particular emphasis on ensuring participant safety. Hence, women who have a positive cytology (HSIL or worse) will be called in and treated according to Tanzanian standard of care. Similarly, women who are persistently HPV positive will be traced, and liquid-based cytology samples will be obtained and analyzed. In case of a positive cytology result (HSIL or worse), the women will be offered colposcopy directed biopsies and treatment according to the cervical cancer screening national guidelines. Informed written consent will be obtained from research participants and confidentiality guaranteed. The trial will be registered at ClinicalTrials.gov and trial analyses and reports will be made in accordance with CONSORT requirements. It is an important part of the study that all women will have a cytology examination when they exit the study after 26 months and we will make sure that all women are cared for in the best possible way.

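### Work package 2 ties the HSIL+ risk to the 26-month cytology, but only persistently HPV positive women get an interim cytology with treatment offered if HSIL+, so an exit-only outcome understates their risk

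*Protocol*

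**What the plan says.** Protocol section 2, second objective, sets out to "examine the absolute risk of HSIL or worse in relation to both one time HPV positivity and HPV persistence", taking HIV status into account.

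Section 3, Work package 2, explains what makes this possible: "Due to the fact that a cytology diagnosis is obtained on all women at the" second follow-up (26 months), "we will also be able to look at the absolute risk of HSIL or worse in relation to both one time HPV positivity", by persistence and by HIV status. The exit cytology is the only outcome source named for this risk.

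The same work package says that women positive for the same type at enrolment and at the first follow-up "will be called in for a cytological examination at the respective clinic". The ethics paragraph at the end of section 3 repeats this: "Similarly, women who are persistently HPV positive will be traced, and liquid-based cytology samples will be obtained and analyzed". It adds that biopsy under colposcopy and treatment are offered if that cytology shows HSIL or worse.

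For other women at month 14 the protocol states HPV testing and genotyping, but no cytology reading. At baseline, women with HSIL or worse and all VIA-positive women are treated. For women who decline to come back to the clinic, "they will be offered screening through a self-collected HPV sample". Expected response is 90% at the first follow-up and 80% at the second.

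**The concern.** Persistence is the exposure under study, and it is also what triggers an earlier search for the outcome, with an offer of treatment if the outcome is found. If risk is read only at month 26, a woman whose HSIL+ was found at recall and successfully treated has a normal exit smear and contributes no event. A woman who cleared the virus is not examined in this way, so any HSIL+ she has is still there to be seen at exit. The loss of events therefore falls on one side of the comparison. The risk in the persistent group is understated, and so is its contrast with women who cleared. If one-time positivity means any positive baseline test, that group contains the persistent women and its risk is understated too, in diluted form.

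At stake is a named objective: how much persistence adds to the risk of severe lesions. An attenuated answer would make persistence look less informative than it is.

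**Working it through.** **The plan's own figures.** The cohort is given as "700 from the screening clinic and 250 from the HIV clinic i.e. ~950 in total", and 700 + 250 = 950 reproduces. The protocol states no event count, sample size or power for the HSIL+ risk. Its only power statement concerns the sensitivity of CareHPV against VIA and is not used here.

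**Size of the recall group.** "We estimate a persistence rate of 40% after 14 months and of 20% after 26 months". With 90% response at month 14, 950 × 0.90 × 0.40 = 342 women; with full attendance, 950 × 0.40 = 380. This takes the 40% as type-specific persistence and does not remove women who already had HSIL+ at baseline, so the group at risk would be somewhat smaller.

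**Exit visits.** At 80% response, 950 × 0.20 = 190 of the 950 would have no exit visit.

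**Illustration of the shortfall.** Three inputs are assumed; none is in the document.
- q: HSIL+ prevalence at the recall cytology, 5–20%
- r: HSIL+ arising between recall and exit in the rest, 3–5%
- u: share of recalled HSIL+ cases that are treated and clear at exit, 50–100%

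Full attendance at recall and exit is assumed, and spontaneous regression is ignored.

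- Cumulative risk = q + (1 − q)r
- Exit-only risk = q(1 − u) + (1 − q)r
- Cases missed = 342 × q × u
- Shortfall = qu ÷ [q + (1 − q)r]

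| q | r | u | Cumulative | Exit only | Missed | Shortfall |
|---|---|---|---|---|---|---|
| 5% | 5% | 50% | 9.8% (33) | 7.3% (25) | 9 | 26% |
| 10% | 5% | 80% | 14.5% (50) | 6.5% (22) | 27 | 55% |
| 20% | 3% | 100% | 22.4% (77) | 2.4% (8) | 68 | 89% |

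The first and last rows are the ends of the range.

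**Effect on the contrast.** Assume a risk of 0.02 + 0.98 × 0.02 = 3.96% in women who are not recalled. With q = 10% and r = 5%, the risk ratio is 0.145 ÷ 0.0396 = 3.7 when recall cases count. Read at exit only, it is 0.065 ÷ 0.0396 = 1.6 at u = 80% and 0.045 ÷ 0.0396 = 1.1 at u = 100%. In the last row of the table it goes from 0.224 ÷ 0.0396 = 5.7 to 0.024 ÷ 0.0396 = 0.6, past no difference.

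The direction needs only that some HSIL+ is found at recall and successfully treated. The size depends wholly on q, r and u.

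**The case against.** The strongest reply is that the protocol never restricts the outcome to the exit smear. It says only that the exit cytology makes the risk analysis possible. The recall cytology is itself a planned result, and event definitions are often left to an analysis plan, which is not at hand here. This aim is also an additional one, with no hypothesis or power attached. Much of that stands: the data needed are planned, and an unseen plan could already count recall cases. It does not remove the point. The protocol gives a reason why the exit cytology serves this objective, and its own recall rule undercuts that reason without comment.

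Four stronger readings are tempting, and the document does not support them.
- A reader might infer that persistent women are treated for persistence. They are recalled for cytology, and treatment is offered only with HSIL or worse.
- A reader might infer that recall cases will be classed as disease-free, or that women with only a self-collected sample will be classed as free of HSIL. No section says either.
- A reader might infer that the comparison by HIV status must be distorted. The protocol gives no persistence rate by HIV status. Distortion follows only if persistence, HSIL+ at recall or treatment uptake differs by HIV status.
- A reader might object that exit cytology on all women contradicts the 80% response. This is mainly wording: the procedure is planned for everyone and the expected response is stated openly.

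It is also fair to object that counting recall cases gives persistent women two looks and the others one, which can inflate the persistent group's risk. This stands and has to be disclosed. A ThinPrep swab is taken from everyone seen at month 14, but no cytology on it is stated for women outside the recall group.

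**Conclusion.** The point holds in limited form. The outcome source named for the absolute HSIL+ risk does not fit a plan in which persistence alone triggers an interim cytology, with treatment offered if HSIL+ is found. Taken as written, an exit-only risk is too low in the persistent group, and its comparison with women who cleared is biased toward no difference. About 342 women are expected to be affected by the recall rule; this is the only figure of size that rests on the protocol's own numbers. The 9 to 68 missed cases, the 26% to 89% shortfall and the risk ratios are illustrations under assumed inputs and are not predictions.

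**What to change.** Define the Work package 2 outcome as first HSIL or worse on any post-baseline study cytology (recall or exit) up to month 26, among women without HSIL+ at baseline, with HSIL+ found at recall counted as an event. In the same text:
- State how women treated at baseline are handled, including those treated because they were VIA positive.
- Report the exit-only result as a sensitivity analysis.
- State that persistent women have two cytology looks and the others one, and that this can bias the result in the opposite direction.
- Treat women with only a self-collected HPV sample, or with no exit visit (about 20% expected), as having missing cytology, and give the expected number with an exit result.

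The cost is wording in the protocol or analysis plan. It needs no new visits, samples or tests, and no change in clinical management. The remaining weakness is the unequal number of looks, which this definition makes visible but does not remove.
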